#### Power analysis

Data from a previous falls prevention trial in the residential aged care setting indicated that falls per resident year (broken into two-month blocks) captured over a 16 month period had a mean (sd) of 2.6 (0.7) [34]. Assuming a similar rate and standard deviation of falls in our present study, our trial across nine facilities will have 85% power to detect an absolute reduction in the rate of falls of 0.7 (this would be a 27% reduction in the rate of falls relative to a baseline of 2.6 falls per resident year).

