#### Steering committees

Within each facility an organisation based steering committee will be established. There are two instances where two facilities are part of one organisation and are indicating a preference for a joint steering committee to be formed, resulting in a total of seven committees. The purpose of each committee is for the research team to consult with key players within the organisation throughout the duration of the project and to keep them informed of project progress and outcomes. Key responsibilities of the committee will include: overseeing the project at an organisation level; monitoring research activities and providing feedback regarding research findings; being a resource to the research team and providing advice from an organisation specific perspective; and discussing strategies for maximising sustainability after project completion.

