### Analysis

Data from the questionnaires and surveys will be analysed using the appropriate non-parametric statistical analyses. Responses to individual items of the survey of safety culture will be compared between groups using ordinal logistic regression analysis, clustering results by the site from which the data was collected.

The rate of falls per resident observed year will be compared between pre intervention and during intervention period using a generalised estimating equation [33]. The monthly number of falls at each facility is the individual unit of measurement. Monthly data by facility will be coded by whether it is collected during the pre-intervention or intervention period. Intervention period data will be additionally coded by whether the data is collected during an "active" intervention period or during an "inactive" intervention period (after completion of the FARGs). Generalised Estimating Equations will be conducted using a Poisson outcome measure distribution family and an exchangeable working correlation structure, though the correlation structure will be checked prior to analysis to determine if the exchangeable structure is still the most appropriate. Adjustment will be made for the number of resident observed years at each site per month. Pre/during intervention and active/inactive intervention variables will be entered into this model as explanatory variables.

For the economic evaluation, the change in costs allocated for the prevention of falls and treatment of fall-related injuries between the pre-intervention and during intervention periods will be the numerator. The change in the number of falls per month (adjusted for resident observed years) will be the denominator, culminating in a cost per fall prevented ratio. Several cost-effectiveness models will be developed by modelling an extended time-line of the project duration for +1, +2, +3, +4 and +5 years beyond the cessation of the implementation phase. The difference between active and inactive period fall rates will be used to guide this modelling. Further sensitivity analyses will be conducted by modelling clinically reasonable variations in the key outcome (falls) and cost (e.g. staffing) measures collected.

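### The stated 85% power matches a normal approximation on nine units with a borrowed block SD; the same inputs give about 75% by a t-test on 8 degrees of freedom

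*Protocol article*

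**What the plan says.** The Power analysis section takes its inputs from an earlier residential-care trial, in which "falls per resident year (broken into two-month blocks) captured over a 16 month period had a mean (sd) of 2.6 (0.7"). It assumes that rate and SD carry over, and concludes that "our trial across nine facilities will have 85% power to detect an absolute reduction in the rate of falls of 0.7", described as a "27% reduction in the rate of falls relative to a baseline of 2.6 falls per resident year". It names no test, significance level, sidedness or pre/post correlation, and does not say that 0.7 is the SD of a within-facility change.

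The Method section describes a pre/post design in all facilities, so each facility is its own comparator. The Analysis section plans a Poisson GEE with an exchangeable working correlation, in which "The monthly number of falls at each facility is the individual unit of measurement". Baseline scoping uses six months of falls data, and the action research groups meet for 12 months.

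**The concern.** The difference and the SD are both 0.7, so the standardised effect is exactly 1. With nine units the test statistic is then centred on √9 = 3, and 3 against 1.96 gives 85% almost exactly. This suggests a large-sample shortcut applied to nine facilities, with the SD of two-month-block rates used unadjusted as the SD of the quantity tested.

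Two things follow. With nine units the variance is estimated on 8 degrees of freedom, and a normal critical value ignores that. In a pre/post comparison the relevant SD is that of the within-facility change, which depends on a correlation that the article does not give.

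This is the article's only power statement. It concerns the falls rate, which carries the project's primary aim and supplies the denominator of the cost per fall prevented. A null result would be read against it.

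**Working it through.** **Inputs.** From Power analysis: n = 9 facilities, SD = 0.7, difference = 0.7, baseline 2.6, stated power 85%. Assumed here because not stated: two-sided α = 0.05. The pre/post correlation ρ is also not stated and is shown over a range.

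**1. Relative effect.** 0.7/2.6 = 26.9%. The 27% is right.

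**2. Reproducing the stated power.** Normal approximation, SD of change 0.7:

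- standard error = 0.7/√9 = 0.233
- 0.7/0.233 = 3
- power = Φ(3 − 1.96) = Φ(1.04) = 85.1%

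**3. Same inputs, t reference distribution.** Noncentral t, 8 df, noncentrality 3, two-sided critical value 2.306: power = 74.8%. The drop of about 10 points comes from the reference distribution alone. Using 1.96 as the cut-off for a t statistic on 8 df would instead give a type I error of about 8.6%.

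**4. Detectable difference.** Solving the 8-df calculation for 85% power with SD of change 0.7 gives 0.80 falls per resident year; 0.80/2.6 = 31%.

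**5. If 0.7 is the SD of each period's rate.** Then SD of change = 0.7 × √(2(1 − ρ)), and the two-sided paired t on 8 df gives:

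| ρ | SD of change | Power |
|---|---|---|
| 0 | 0.990 | 46% |
| 0.3 | 0.828 | 60% |
| 0.5 | 0.700 | 75% |
| 0.62 | 0.610 | 85% |
| 0.7 | 0.542 | 92% |

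Under this reading, using 0.7 directly as the SD of change amounts to assuming ρ = 0.5.

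**6. Bearing on the planned analysis (illustration).** Suppose 0.7 is the SD of one two-month block, and each facility contributes 3 pre-intervention blocks (six months) and 6 active blocks (12 months). With ρ = 0 and the same effect everywhere:

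- SD of change = 0.7 × √(1/3 + 1/6) = 0.495; power 96% (t, 8 df)
- true effect varying between facilities with SD 0.35: √(0.495² + 0.35²) = 0.606; power 86%
- true effect varying with SD 0.5: √(0.495² + 0.5²) = 0.704; power 74%

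The article gives neither the correlation nor the variation in effect, so it does not say which case applies.

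**The case against.** The strongest reply is that the trial will not run a t-test on one change per facility. It will fit a GEE to repeated monthly counts, and averaging over months can bring power well above 85%, as step 6 shows. The facilities were also chosen to differ in care level and resident group; stable differences between them would plausibly raise the pre/post correlation, and above about 0.62 even the paired t exceeds 85%. This stands. It means that 75% is not the power of the planned analysis, and that the error could run either way.

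A reader might infer that the 85% can only come from testing nine facilities against a known baseline of 2.6. The article does not support that. A paired z-test with an estimated baseline and SD of change 0.7 gives the identical 85.1%, and a one-sided 5% t-test on 8 df gives 86.2%.

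A reader might also treat 75% as a ceiling. With 0.7 as the per-period SD, that holds only for correlations up to about 0.5.

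Finally, the Steering committees section notes that "There are two instances where two facilities are part of one organisation", which might suggest seven independent units and about 60% power (t, 6 df, SD of change 0.7). That requires total dependence within each pair. Each facility has its own action research group and action plan, so 60% is an extreme bound.

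It may also be said that a condensed article leaves test and alpha to a fuller document. That excuses their absence, but the article does assert a definite power figure together with its inputs, and the figure can be checked against them.

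**Conclusion.** The point holds in a limited form. The stated 85% agrees with a two-sided normal approximation on nine units using an SD of change of 0.7. On those inputs, allowing for 8 degrees of freedom gives 74.8%, or 85% power for a reduction of about 0.80 (31%). If 0.7 is the SD of each period's rate, the range is 46% to 92% for correlations from 0 to 0.7, too wide for an unqualified claim.

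This rests on two-sided α of 0.05 and one pre/post change per facility. What the 0.7 varies over (blocks, facilities or both) depends on a cited source that is not available here. The document does not show that the design falls short of 85%, because the power of the monthly GEE cannot be derived from it. The figure is unsupported as stated. Severity is moderate: no site, data item or analysis has to change.

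**What to change.** Rewrite the Power analysis paragraph so that it:

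- states the test, alpha and sidedness;
- says that 0.7 is the SD of two-month-block rates in another trial, used as a stand-in for the SD of the within-facility change;
- gives about 75% power for a reduction of 0.7, or 85% for about 0.80 (31%), under an SD of change of 0.7 with 8 df;
- shows the range over pre/post correlation (46% at 0, 75% at 0.5, 85% at about 0.62, 92% at 0.7, if 0.7 is the per-period SD);
- either bases the figure on the GEE with nine clusters, giving the numbers of pre-intervention and intervention months, the within-facility correlation and the assumed variation in effect between facilities, or labels it approximate.

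Possible wording for the approximate version:

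> Taking 0.7 as the SD of the within-facility change, nine facilities give about 75% power (paired t-test, 8 df, two-sided 5%) for a reduction of 0.7 falls per resident year, or 85% power for a reduction of about 0.80 (31%). The 0.7 is an SD of two-month-block rates used as a stand-in. If it is the SD of each period's rate, power for 0.7 ranges from 46% to 92% as the pre/post correlation goes from 0 to 0.7. These figures are approximate; the planned analysis of monthly counts may have higher or lower power.

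The cost is one paragraph and a less favourable stated power. No extra sites are needed.

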### Ethics

This project was approved by local human research ethics committees for each site (Ballarat Health Service & St John of God Human Research Ethics Committee; Toowoomba & Darling Downs Health Service District Human Research Ethics Committee; Human Research Ethics Committee St Vincent's Hospital; Tasmania Social Sciences Human Research Ethics Committee).

All staff in each facility will be provided with a Plain Language Statement and Consent Form inviting their participation in the study (for example, training, focus groups, FARGs, surveys, reviews of various documents and tools).

Managers and/or FRNs will identify residents who will be able to give informed consent and provide them with a Plain Language Statement and Consent Form to obtain consent for various components of the project that are outside usual care, such as audits to their rooms, additional falls risk assessment, or implementation of safety devices such as hip protectors. For those residents unable to provide informed consent due to cognitive impairment, facility staff will provide relatives/contact persons with a Plain Language Statement and Consent Form to seek consent for participation on behalf of their family member residing in the participating facility.

## Discussion

Despite the availability of evidence-based guidelines for implementing falls prevention interventions in residential aged care, there is moderate evidence that these interventions are not routinely incorporated into routine practice. This project aims to provide a comprehensive multifaceted strategy to try to increase uptake of evidence based guidelines in the participating facilities. In line with the research evidence, a multi-factorial, individualised (to the specific requirements of each facility) and all of facility approach is planned to develop and implement an action plan based on the best available evidence in the participating facilities. We will explore the effectiveness of this approach in a range of facilities including dementia specific and psychogeriatric, in which there is limited research of effective approaches to falls prevention.

An action research approach will be used to assist in engaging staff in practice change, encouraging them to identify better practice strategies, implement and evaluate the outcomes in their own practice. It is anticipated that this approach will be useful for empowering staff and facilitating sustainable evidence based falls prevention interventions.

The collection of falls data, and an economic evaluation determining the costs of the implementation and modelling of potential cost savings through the impact of project activity will also inform whether there are economic benefits of investing in these activities. With these data, other RACFs would find it more compelling to follow a similar approach to falls minimisation.

There are numerous factors that may limit the uptake of best practice falls prevention guidelines in RACFs, including lack of knowledge among staff, residents and families that many falls are preventable and the type of interventions that can be effective; lack of optimisation of staff routines and practice; unsupportive/unsafe environments; lack of adequate falls incident reporting and analysis at the local level; and lack of staff time. This multi-factorial approach, inclusive of staff as key drivers within each facility, will implement an evidence based falls prevention project across nine Australian RACFs that aim to reduce falls and falls-related injuries.

## List of abbreviations used

RACF: Residential Aged Care Facility; FRN: Falls Resource Nurse; EFT: Equivalent Full Time; FARG: Falls Action Research Group; RPPE: Revised Professional Practice Environment Scale; FROP-RC: Falls Risk for Older People - Residential Care.
